### Recruitment of women to the trial

Recruitment to the trial will take place in the antenatal clinic when women attend for their maternity booking visit.

#### Participant information

Women will be sent written information (a brochure) about the study when they ring to book into the hospital for their pregnancy care (see Additional file 1). A participant information sheet and another copy of the brochure will be given to each woman at the time of recruitment. Women will be given the opportunity to read the information sheet, think about the study, and then consent if they wish.

#### Informed consent

Written consent will be obtained if a woman agrees to enter the study. This will be witnessed and signed by another person, as well as the research midwife.

#### Assessment of eligibility

Research midwives will liaise with midwifery and clerical staff in the antenatal clinics to obtain daily booking visit lists. A preliminary assessment of a woman's study eligibility will be made by checking the woman's medical record.

#### Recruitment protocol

Women will be approached prior to or immediately after completion of the midwife booking visit. Research midwives will follow a recruitment guide after determining that a woman is potentially eligible.

If a woman does not wish to decide immediately, she will be provided with study contact details, a copy of the consent form and background questionnaire, and a reply paid envelope. To join the study she can then contact the research midwife and return the forms by mail. Upon the return of the forms, the woman will be randomised and contacted regarding the outcome of the random allocation.

### Intervention allocation

#### Randomisation procedure

The randomisation system in use for the trial was developed by the Australian National Health and Medical Research Centre Clinical Trials Centre . An Interactive Voice Response System (IVRS) activated by telephone will be used for randomising women to the two treatment arms of the trial (i.e. standard care and caseload midwifery care).

Randomisation will be undertaken using stratified permuted blocks of varying size, with randomisation stratified by parity (i.e. first or subsequent birth). For each woman, the system will assign the treatment in the next available sequential slot in the appropriate list of blocks.

When a woman agrees to enter the study the research midwife will complete a COSMOS study specific Trial Randomisation IVRS Worksheet with details that the system will request to complete the randomisation procedure (e.g. woman's full initials, parity and date of birth). Access to the IVRS is achieved by dialing a toll-free telephone number and navigating to the COSMOS trial via a menu system. The system is designed so that no woman can be randomised twice. A back-up system is in place in case of a system failure, via a nominated person at the Clinical Trial Centre. After completing all prompts the woman will be allocated a study number and treatment arm. The woman will be informed immediately of the randomisation outcome and further maternity care bookings arranged accordingly.

### Study participation

#### Baseline

After consenting to participate in the study and prior to randomisation, women will be asked to complete a baseline questionnaire, which includes demographic data.

#### Intervention

Women will be allocated to either the control or intervention arms (described below).

#### Follow-up

Further data collection is scheduled to take place following the birth (obstetric and medical data obtained from hospital record) and self-completed participant questionnaires at two and six months postpartum (postal). The hospital records will be checked following the birth before sending postal questionnaires to minimise the chance of a woman who has experienced a fetal death or an early neonatal death receiving a questionnaire. Women who are seriously ill or who have had a seriously ill infant will be sent questionnaires subject to confirmation that they have been discharged from hospital in good health. Where there are any concerns regarding whether a woman should be sent a questionnaire, the research team will discuss the issue and reach agreement.

#### Study completion

Successful completion of the study occurs after the six-month questionnaire is returned. If desired, women will be sent a summary of the results after completion of the analyses.

#### Participant discontinuation

Women are free to withdraw from the study at any time. No further study follow-up will occur.

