## Methods/design

The study uses a two arm, unblinded randomised controlled design, stratified by parity, to compare caseload midwifery care with standard maternity care.

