### Outcome variables

#### Primary outcome

The principal outcome of the study is the proportion of women having a caesarean section birth.

For the secondary aims of the study the following variables will be collected:

a) Instrumental vaginal births

b) Obstetric analgesia

c) Perineal trauma

d) Induction of labour and augmentation of labour

e) Satisfaction with care

f) Proportion of women breastfeeding to two and six months

g) Postnatal depression

h) Smoking

i) Costs

j) Staff attrition and satisfaction

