#### Description of standard care

Women allocated to the control group can choose from the standard hospital options for low risk women; these include midwifery-led care – which may involve some continuity or could mean women seeing a different midwife for every visit; care by junior medical obstetric staff; or community based care – usually shared care with an accredited general medical practitioner (GP) (i.e. the GP provides the majority of the woman's antenatal care, usually nearer to her home, but the woman is booked for labour, birth and postnatal care at the hospital). In both the midwife-led and GP-led models women would be booked to see an obstetrician at 36 and 42 weeks gestation, with other referral or consultation as necessary. When women come into the hospital for labour, birth and postnatal care they will be cared for by whichever midwives and doctors are rostered for duty. Care will be provided according to the same hospital guidelines and protocols as for the women in the intervention arm.

It is possible that some women allocated to either the intervention or the control group will seek other care options, such as care with a private obstetrician or midwife, but neither of these is available at the Royal Women's Hospital. In this event we aim to obtain all data as planned, and analysis will be by intention-to-treat.

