### Data collection

#### Trial participants

○ A background demographic data questionnaire will be completed by women at the time of recruitment, prior to randomisation.

○ Obstetric/medical data will be collected manually from the medical record following the birth.

○ Data will be collected at two and six months postpartum by postal survey. Questionnaires will be mailed by the research midwives and/or project coordinator. A covering letter will be sent with each questionnaire and a reply paid envelope included. To maximise response, a reminder letter will be sent two weeks after the first mailing, then if there is no response in another two weeks women will receive a second reminder letter that includes another copy of the questionnaire. When these questionnaires are returned they will be checked for women's responses to the self harm question (Q10) on the Edinburgh Postnatal Depression Scale [49], and if a woman has indicated that the thought about harming herself has occurred to her "quite often" in the last week she will be telephoned according to a pre-specified protocol (see Additional file 3).

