### Data analysis

#### Quantitative analysis

This will be undertaken using STATA [51] and data will be collected to meet the CONSORT guidelines for reporting of randomised trials.

The first stage of analysis will check the comparability of participants allocated to the two groups. The intervention group will be compared with the standard care group by intention to treat analysis. Proportions of women having a caesarean section will be compared using chi-square tests and odds/risk ratios. Comparison of means will be undertaken for continuous variables using t-tests where data are normally distributed or medians compared using Mann-Whitney U tests otherwise. Ranked or Likert-type scales will be analysed using cumulative odds ratios. Where there are differences in baseline characteristics of the women in the two groups which might be associated with outcomes, an additional multivariate analysis will be carried out.

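### The withdrawal rule, read with the plan's own account of follow-up, stops collection of mode of birth for women who leave the study before their birth record is abstracted

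*Protocol article*

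**What the plan says.** The rule under Participant discontinuation is two sentences long: "Women are free to withdraw from the study at any time. No further study follow-up will occur". It gives no levels of withdrawal.

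The Follow-up section of the protocol article describes what follow-up consists of. It begins with the birth data: "Further data collection is scheduled to take place following the birth (obstetric and medical data obtained from hospital record". The postal questionnaires at two and six months come after that. The data collection section repeats the source: "Obstetric/medical data will be collected manually from the medical record following the birth". The primary outcome rests on that record: "The principal outcome of the study is the proportion of women having a caesarean section birth".

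Two further provisions bear on the point. The Quantitative analysis section says: "The intervention group will be compared with the standard care group by intention to treat analysis". For women in either arm who seek care elsewhere, the section on standard care says: "In this event we aim to obtain all data as planned, and analysis will be by intention-to-treat".

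The trial is open: "The study uses a two arm, unblinded randomised controlled design, stratified by parity". Allocation is disclosed at once: "The woman will be informed immediately of the randomisation outcome and further maternity care bookings arranged accordingly". Recruitment is before 24 completed weeks of gestation, so a long interval separates allocation from outcome.

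**The concern.** Mode of birth is read from the hospital record and asks nothing of the woman. A rule that ends all follow-up on withdrawal gives up this outcome along with the questionnaires, although only the questionnaires need her cooperation. The rule does not separate a woman who wants no more post or telephone calls from one who refuses use of her record.

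The trial is unblinded and the arm is known long before birth, so the decision to withdraw can depend on the arm, for example through disappointment at being allocated care that was available anyway. If withdrawers also differ in their caesarean risk, the comparison of those who remain is biased. The 10% loss allowance protects power but does nothing against this bias. An analysis plan cannot repair it, because the data would never have been collected.

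**Working it through.** **1. Which women are affected**

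| Situation | Provision | Mode of birth still sought? |
|---|---|---|
| Seeks other care, stays in the study | Description of standard care | Yes, analysed as randomised |
| Does not return questionnaires | Data collection: two reminders; record abstraction is a separate item | Yes |
| Withdraws from the study after abstraction | Participant discontinuation | Already held; the rule is silent on held data |
| Withdraws from the study before abstraction, objecting only to questionnaires or contact | Participant discontinuation with Follow-up | No |
| Withdraws and refuses use of her record | Participant discontinuation | No, and rightly so |

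The defect lies in the fourth row only.

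**2. The plan's own sample size**

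Inputs from the Sample size section: 19% v 14%, 80% power, 95% confidence (read as two-sided 5%). With p̄ = 0.165:

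n = [1.96·√(2·0.165·0.835) + 0.8416·√(0.19·0.81 + 0.14·0.86)]² / 0.05² = 864 per arm without continuity correction.

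With the correction, (n/4)·[1 + √(1 + 4/(0.05n))]² = 904 per arm, which matches the plan. For 10% loss, 904/0.90 = 1004.4, stated as 1004, or 2008 in total. These figures stand.

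**3. Power if every birth outcome were kept**

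Power = Φ{[0.05 − 1/n − 1.96·√(0.27555/n)] / √(0.2743/n)}

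- n = 904: Φ(0.0147/0.0174) = 80.0%
- n = 1004: Φ(0.01653/0.01653) = 84.1%

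The second figure is a ceiling. It assumes no loss of any kind.

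**4. Bias: an illustration on assumed inputs**

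The documents give neither withdrawal rates nor caesarean rates among withdrawers. Let w be the proportion withdrawing, r the caesarean rate among withdrawers (taken as equal in both arms) and p the true rate. The rate among those who remain is (p − w·r)/(1 − w).

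Take no true effect, p = 19% in both arms, r = 29%:

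- Standard care, w = 8%: (0.19 − 0.0232)/0.92 = 18.1%
- Caseload, w = 2%: (0.19 − 0.0058)/0.98 = 18.8%

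The spurious difference is 0.67 points against caseload, 13% of the 5-point target. From 1004 per arm, 1004 × 0.92 = 924 and 1004 × 0.98 = 984 women remain. The standard error is then about 1.78 points, so the bias is about 0.37 standard errors, and the null is rejected about 6.6% of the time instead of 5%.

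**5. Range, with r from 5% to 40%** (1004 randomised per arm, no continuity correction; difference is standard care minus caseload)

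| Withdrawal, standard v caseload | No true effect: spurious difference | Rejection rate | True 19% v 14%: observed difference | Power |
|---|---|---|---|---|
| 5% v 1% | +0.6 to −0.9 points | 5.0% to 8.0% | 5.7 to 4.2 points | 91% to 71% |
| 10% v 2% | +1.3 to −1.9 points | 5.0% to 19.1% | 6.4 to 3.2 points | 96% to 49% |

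The lowest rejection rate, 5.0%, occurs at r = 19%, where withdrawers do not differ from the rest. With equal withdrawal in both arms and the same r, there is no bias under the null. The bias can run in either direction.

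**The case against.** The strongest reply is that the rule covers only women who leave the study itself. Those who dislike their arm and go elsewhere, and those who ignore the questionnaires, are already provided for. This stands, and it removes much of the route by which disappointment could cost outcomes. A reader might infer that every woman unhappy with her allocation loses her outcome; the documents do not support that.

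Secondly, a reader might infer that data already collected are thrown away, or that the rule contradicts the intention-to-treat statement. Neither follows. The rule speaks of further follow-up and says nothing about data in hand. Honouring a withdrawal creates a missing outcome but moves no woman between arms.

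Thirdly, an article condenses. Levels of withdrawal may be set out in the information sheet or consent form, which are not at hand, and follow-up might mean contact only. The first part is fair as far as it goes, but the article does not merely omit a detail. It states a rule, and its own Follow-up section places hospital-record data inside that term. The contact-only reading is not the one the text supports.

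Fourthly, the bias figures rest on chosen withdrawal rates, and the main example runs against caseload, so it would not create a false claim of benefit. Both remarks are correct. The power gain is likewise an upper bound. Some women may move to private care not offered at this hospital, and some withdrawers will refuse record use. The 904 per arm also serves six-month questionnaire outcomes, where loss is to be expected.

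**Conclusion.** The point holds in a limited form. As written, the plan does not collect the primary outcome for women who formally withdraw before their birth record is abstracted, including those who would have allowed its use. This weakens the intention-to-treat comparison through avoidable and possibly arm-dependent missing data.

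The size cannot be known from the documents. On the assumption of 8% v 2% withdrawal and 29% caesareans among withdrawers, the bias is about 0.7 points. It becomes material only if withdrawal is both frequent and unequal between arms, as at the extremes of the 10% v 2% range. Full retention would raise power from 80% to at most 84%. No stated figure is wrong, and the sample size is adequate for its stated purpose. The case for change is that the remedy is cheap.

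**What to change.** Amend the rule under Participant discontinuation, together with the consent and withdrawal wording, as follows:

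- Separate withdrawal from questionnaires or contact from refusal of record use.
- Unless a woman refuses record use, abstract mode of birth and the other obstetric outcomes and analyse her in her allocated arm.
- Keep data collected before withdrawal, as far as consent allows.
- Report the number of withdrawals at each level by arm.

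The cost is a minor ethics amendment and revised forms. Record abstraction is already planned, so no new procedure is needed and the sample size does not change. A woman who refuses use of her record remains free to do so, and some primary outcomes will still be missing for that reason.

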### Interventions

#### Description of caseload care

Women allocated to the caseload intervention will receive antenatal, intrapartum and postpartum care from a primary caseload midwife with one or two antenatal visits to be conducted by a 'back-up' midwife. The primary midwife will be on call for the woman's labour and birth except in designated circumstances such as annual leave; sick leave; having already worked more than 12 hours in a 24 hour period; having more than one woman in labour; or if it is on one of the two days per week that the primary midwife is scheduled to not work or be on call. Care will then be provided by a back-up midwife or on occasion by non-caseload midwives. Negotiation of these details will be organised within each caseload group, as autonomy and control over working times and conditions have been shown to be important aspects of preventing burnout [24]. The primary midwife will collaborate with obstetricians and other health professionals as necessary, and will continue to provide caseload care in addition to care provided by obstetricians if complications develop. In addition to providing care until after the birth of the baby, the primary midwife (or a back up midwife) will attend the hospital on most days to provide some postnatal care and will provide domiciliary care following discharge from hospital. Care will be provided according to hospital guidelines and protocols.

#### Recruitment of midwives to caseload

Approximately 12 fulltime midwives are required to staff the intervention. This can consist of more actual midwives (e.g. it could be several part time midwives). Positions will be advertised in the first instance internally, then if the required number is not met there will be external advertisements. To be eligible, midwives need to have completed two years clinical midwifery post-registration.

#### Education of caseload midwives

In addition to any education deemed to be necessary by the hospital in preparation for working in the caseload model, caseload midwives will be offered a one day training session by the research team. One third of the day will focus on the research components of the trial and the rest will be in regard to working in this new way-practicalities, personal boundaries, and working in a small group (see Additional file 2 for program outline).

#### Description of standard care

Women allocated to the control group can choose from the standard hospital options for low risk women; these include midwifery-led care – which may involve some continuity or could mean women seeing a different midwife for every visit; care by junior medical obstetric staff; or community based care – usually shared care with an accredited general medical practitioner (GP) (i.e. the GP provides the majority of the woman's antenatal care, usually nearer to her home, but the woman is booked for labour, birth and postnatal care at the hospital). In both the midwife-led and GP-led models women would be booked to see an obstetrician at 36 and 42 weeks gestation, with other referral or consultation as necessary. When women come into the hospital for labour, birth and postnatal care they will be cared for by whichever midwives and doctors are rostered for duty. Care will be provided according to the same hospital guidelines and protocols as for the women in the intervention arm.

It is possible that some women allocated to either the intervention or the control group will seek other care options, such as care with a private obstetrician or midwife, but neither of these is available at the Royal Women's Hospital. In this event we aim to obtain all data as planned, and analysis will be by intention-to-treat.

### Process evaluation

Adherence to the study protocol will be monitored and intervention fidelity measured in a range of ways.

#### Measures of intervention exposure

Data regarding the extent to which care was provided by the primary midwife will be collected from the medical record following the birth and from the women via postal questionnaire at two months. To assess and compare continuity of carer, women in both trial arms will be asked about the presence of known care providers for labour, birth, postnatal hospital care and domiciliary care.

#### Caseload midwife meetings

Monthly team meetings will be held with the caseload midwives and a member of the research team (DF) to provide support and give an opportunity for problem-solving and debriefing. The research team member will be available to the caseload midwives before and after meetings and will be contactable between meetings by email or telephone. Protocol adherence will be discussed at team meetings. Other key support for the caseload midwives will be from their clinical manager(s) as well as from the Director of Maternity Services (TF).

#### Adherence to protocols

Three sources will contribute to assessing adherence to the intervention protocols: interviews with the intervention midwives at the beginning and end of the trial; monthly meetings between the caseload midwives and the research team member; and data collection from the medical records.

#### Intervention evaluation by participants

The postal questionnaire sent to women at two months will include a number of questions about women's model of care and continuity of carer. Questions will also assess satisfaction with model of care provision.

#### Intervention evaluation by caseload midwives, non-caseload midwives and other key stakeholders

Comprehensive evaluation of how the intervention works within the organisation will be undertaken using surveys and key informant interviews.

### Data collection

#### Trial participants

○ A background demographic data questionnaire will be completed by women at the time of recruitment, prior to randomisation.

○ Obstetric/medical data will be collected manually from the medical record following the birth.

○ Data will be collected at two and six months postpartum by postal survey. Questionnaires will be mailed by the research midwives and/or project coordinator. A covering letter will be sent with each questionnaire and a reply paid envelope included. To maximise response, a reminder letter will be sent two weeks after the first mailing, then if there is no response in another two weeks women will receive a second reminder letter that includes another copy of the questionnaire. When these questionnaires are returned they will be checked for women's responses to the self harm question (Q10) on the Edinburgh Postnatal Depression Scale [49], and if a woman has indicated that the thought about harming herself has occurred to her "quite often" in the last week she will be telephoned according to a pre-specified protocol (see Additional file 3).

